### Phase 2: intervention evaluation

#### Study activities

Training and usability testing will be followed by supported implementation and evaluation (early-stage effectiveness-implementation trial).

#### Informed consent

mNavigator will be used as the standard of care for patient intake and outcome tracking of pediatric cancer patients at BMC. All pediatric cancer patients at BMC will be registered and tracked in mNavigator. For research purposes, research staff (e.g., research coordinator, mNavigator users, etc.) will consent caregivers of any patients who receive a clinical diagnosis of Rb or BL for tracking their treatment information. Data for only those providing informed consent will be used in the research study (with the exception of historical data). For consenting patients, mNavigator will be used for treatment management with a typical treatment duration of 3 months for patient with BL and 4 months for patient with Rb.

#### Data collection

There will be mixed methods data collection including semi-structured qualitative interviews and a quantitative survey including validated measures such as Organizational Readiness for Implementing Change (ORIC) [29].

##### Quantitative data collection

To measure compliance with standardized pediatric oncology protocols, we will use personal and clinical data points routinely collected as part of clinical visits along with the data entered into mNavigator.

We will compare treatment protocol compliance between BL/Rb retrospective patients (treated between 2015 and 19 when standardized treatment protocols for BL and Rb were introduced at BMC, but before introduction of mNavigator) and BL/Rb prospective patients (treated using mNavigator). To collect retrospective medical record data, trained research staff will abstract medical data into mNavigator from paper records for patients diagnosed with BL and Rb between 2015 and 19. Items abstracted will include as many data points available in paper records that are included in mNavigator.

To assess factors that may facilitate or inhibit implementation of the system and inform scale-up and design of future studies, we will periodically conduct observations, or use surveys and/or checklists to collect data related to the following areas:
Technical functionality (such as content, time to complete forms)Technical stability (network connectivity, server downtime, failure and errors; issues with quality of data and system, device damage)Fidelity and quality of system implementation. These data will help us assess and describe the fidelity of the intervention (how mNavigator was used in practice and whether protocol steps were followed

##### Qualitative data collection

We will invite mNavigator users to complete a 30–45 min in-depth interviews to discuss system acceptance and usability, and satisfaction. Using the validated ORIC measure, we may also revisit the degree of change in readiness and commitment over time to use mNavigator and change in efficacy, a belief in the capacity at BMC to implement mNavigator.

We will also reach out to parents or caregivers of pediatric oncology patients to conduct in-depth qualitative interviews to explore factors that may contribute to treatment abandonment (barriers and facilitators to initiating or completing treatment). Participants will be able to choose to complete the interview in Swahili or English. Interviews will be transcribed verbatim. Those interviews conducted in Swahili will be translated into English.

We will document activities contributing to increased research capacity at BMC. Examples of research capacity include: (a) technology transfer and research capacity for implementation of digital health interventions among BMC investigators through collaborations with Duke and Dimagi Inc.; (b) continued development of research management capacity through weekly conference calls between project coordinators regarding budget management, quality assurance oversight, and local staff leadership. We will also document the process of training and ongoing support provided to mNavigator users.

### Participants

The following two groups of participants will be identified and screened for eligibility.
*BMC health professionals and staff:* We will approach BMC personnel, both who will directly use mNavigator and/or those whose work will be impacted by mNavigator, to offer enrollment in the study to help test the usability of the mNavigator system or provide general feedback prior to implementation and during implementation. BMC personnel will include health professionals who provide routine clinical care for pediatric cancer patients such as patient navigators, clinical coordinators, health providers and other clinical staff as well as non-clinical staff and other key stakeholders whose buy-in will be necessary for the successful implementation of mNavigator. Health professionals and staff will be identified to participate in this study based on the following inclusion criteria:Must be a health provider or staff working at BMC who provide care or support clinical care for cancer patients at BMC (medical oncologists, radiation oncologists, nurses, patient navigators, clinical coordinators, among others), or other key stakeholder.Must be 18 years or older at the time of informed consent.2.*Parents or caregivers and their child who is a BMC pediatric oncology patient with diagnosis of BL or Rb*

As part of standard of care for patient intake, mNavigator will be used to register new BMC pediatric oncology patients yearly. Over the course of 1 year, patients with a diagnosis of BL or Rb will be followed for the duration of treatment (typically 3 months for BL and 4 months for Rb) using mNavigator. Eligible participants are:
Patients with suspected or known diagnosis of either BL and RbPatients younger than 18 years of age at enrollment

### Informed consent

Since all patients enrolled in the study will be children younger than 18 years old at the time of diagnosis, written consent will be obtained from parent, guardian or caregiver (see Additional file 2 for example consent). Assent will be sought for children who are 6 years old or older. Patients who turn 18 years of age during active study participation will be re-consented as adults. After explaining the purpose of the study, as well as the process, consent will be obtained in writing or verbally (with thumbprint in the presence of a literate witness), depending on participant’s literacy. Comprehension of the information provided will be ensured by asking potential participants if they completely understand the project aim and process. Research staff will also ask participants to repeat, in their own words, what they understand about the research study and how we are asking them to participate. These methods to ensure comprehension and avoid unintentional coercion will be taught to research staff prior to conducting any consents.

### Sample size and recruitment

Sample size estimates are based on the patient volume at BMC. Based on prior experience, approximately 150 new pediatric patients present each year for cancer management at BMC. Of these, approximately 50 patients are anticipated to have a diagnosis of BL or Rb. All new patients will be registered in mNavigator, and all patients with BL and Rb who provide informed consent will be tracked in the system for treatment management. Historical data is anticipated to be available for approximately 200 BL and Rb patients from 2015 to 2019 (i.e., 50 records/year). All available historical data will be used in the comparator arm. Similarly, approximately 15 health professionals at BMC are identified as individuals directly or indirectly impacted by mNavigator, all of whom will be approached for study participation. All prospective participants will be approached in person to provide study information and invite participation.

To ensure thematic saturation of qualitative data and that diverse perspectives are heard, we will complete an interview with parents of at least 12 BL and 12 Rb patients. Interviews may be recorded using an encrypted digital device.

### Outcome measures

Study outcomes are summarized in Tables 3 and 4. Measurement of study outcomes is guided by the RE-AIM framework. In mNavigator, we will collect data points that will allow us to measure outcomes in the following domains:
Reach – e.g., proportion of eligible patients for whom protocol was used.Effectiveness – e.g., proportion of cases that abandoned care, with treatment completion and time from hospital presentation to confirmed diagnosisAdoption – e.g., proportion of providers who use the protocol, provider acceptability and satisfaction with mNavigator content, ease of delivery and credibilityImplementation/Compliance – e.g., proportion of protocol steps completed per patientMaintenance (measured in future studies)

**Table 3 Tab3:** Summary of outcomes related to intervention effectiveness and their measurement

Outcome	Measure	Data source
Change in protocol compliance (primary outcome)	Percent difference in protocol compliance with mNavigator and historical compliance. Protocol compliance is calculated as proportion of protocol steps completed, based on a compliance checklist.	mNavigator data from prospectively registered pediatric cancer patients from July 2019 – July 2020 and data extracted from paper charts for patients registered at BMC from 2015 – June 2019 entered into mNavigator
Change in treatment abandonment (secondary outcome)	Calculated as the difference in proportion of patients registered in mNavigator who abandoned treatment compared to historical controls who abandoned treatment. Treatment abandonment is defined as missing four or more consecutive weeks of treatment or follow-up while still on therapy.	Data from mNavigator (outcome form)
Change in treatment completion rate	Calculated as the proportion of patients registered in mNavigator who completed treatment compared to historical controls	Data from mNavigator (outcome form)
Change in time to diagnosis	Change in the number of days to diagnosis using mNavigator compared to historical controls. Time to diagnosis is computed as the duration from registration to diagnosis	Data from mNavigator (registration form; diagnosis form)

**Table 4 Tab4:** System-level outcomes related to the mNavigator application

Outcome	Measure	Data source
Usability^a^	System usability scale score ranging from 0 to 100. A SUS score above a 68 is considered above average and anything below 68 is below average.	10-point validated system usability scale
Acceptability	Proportion of providers who would continue to use the app. Proportion of providers who would recommend the app to others.	Semi-structured interviews
Utilization	Number of forms submitted, stratified, by users, per month of implementation	Data from mNavigator (Mobile users statistics)
Reach	Number of patients registered in mNavigator during study period	Data from mNavigator (Mobile users statistics)
Stability	• Number of instances of mNavigator failure per month (all-causes) • Number of instances of CommCare failure per month (all-causes) • Number of instances of device • failure per month (all-causes)	Data from CommCare (Worker Activity and Daily Activity reports) cross checked with manual reports from Mobile users
Training	Number of hours of initial training as well as hours of ongoing support provided during the first month of Implementation	Manually recorded from Duke team members that are performing initial training
User-proficiency	Number of users who are proficient in use of mNavigator within first month of implementation	Data from CommCare (Worker Activity reports)
Time per form	Average time in minutes spent completing each form, stratified by form	Data from mNavigator (Mobile users statistics)
Time per patient	Total time in minutes spent entering patient data in mNavigator, from time of registration until an outcome is recorded. Calculated by summing time for completing each form by patient.	Data from mNavigator (Mobile users statistics)

^a^System Usability Scale developed by John Brooke is available from www.usability.gov

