### Study aims

This early-stage effectiveness-implementation hybrid study has two primary aims:

Aim 1. To develop mNavigator by adapting an open-source digital health case management platform, CommCare, to incorporate protocol-driven treatment for pediatric cancer.

Aim 2. To evaluate the effectiveness of mNavigator for improving provider compliance with protocol-driven treatment for pediatric cancer and reducing treatment abandonment.

A secondary aim of the study is to understand factors that facilitate or inhibit the implementation of mNavigator in tertiary care settings for pediatric cancer.

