#### Intervention delivery

The users will use mNavigator during one-on-one interactions with patients and their caregivers. At the first interaction with each cancer patient, the users will register the patient. During subsequent interactions, users will:
Enter pre-diagnostic labs and imaging tests.Assign patients based on physician preliminary clinical evaluation to BL, Rb, or non-BL/Rb cohorts for further assessment.Complete and review pre-treatment staging and laboratory checklists for patients with preliminary Rb or BL diagnosis to facilitate protocol compliance.Deliver cancer educational information in video format.Review treatment guidelines with decision support algorithms to facilitate care coordination between mNavigator users and prescribing physicians.Enter information on changes in treatment plan, including referrals to outside hospitals, second line treatment, or palliation.Follow-up with patients to record health related outcomes (on treatment, off therapy, relapsed disease, etc.) and vital status.

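### On its plain reading, the abandonment outcome cannot count a child with BL or Rb who never starts treatment, so it can rise while total loss to treatment falls

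*Protocol article*

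**What the plan says.** Aim 2 (Study aims) is: "To evaluate the effectiveness of mNavigator for improving provider compliance with protocol-driven treatment for pediatric cancer and reducing treatment abandonment". Abandonment is the outcome that Table 3 (Outcome measures) labels secondary.

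Table 3 gives the event: "Treatment abandonment is defined as missing four or more consecutive weeks of treatment or follow-up while still on therapy". It gives the comparison as: "Calculated as the difference in proportion of patients registered in mNavigator who abandoned treatment compared to historical controls who abandoned treatment".

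Entry to the system is early. Intervention delivery states: "At the first interaction with each cancer patient, the users will register the patient". Diagnostic work-up, assignment to BL or Rb, and treatment come afterwards.

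Qualitative data collection describes the caregiver interviews as a way to "explore factors that may contribute to treatment abandonment (barriers and facilitators to initiating or completing treatment"). So the interviews look at starting treatment as well as finishing it.

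The next row of Table 3 is the completion rate: "Calculated as the proportion of patients registered in mNavigator who completed treatment compared to historical controls".

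No section says how a diagnosed child who never starts is classified for the abandonment outcome.

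**The concern.** The Table 3 rule requires the child to be on therapy when the four-week gap occurs. A family that leaves between diagnosis and the first treatment never meets that condition. The child stays in the denominator, because registration has already happened, and is treated as not having abandoned.

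The measured outcome is thus narrower than the subject of the interviews. It also depends on how many families start. If more start in the mNavigator period, more children are exposed to the risk of a counted event, while losses that were invisible before treatment disappear without credit. The reverse also holds: if losses move to before the first treatment, the written measure looks better. Either way, the difference between cohorts could mislead on a stated aim.

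**Working it through.** The plan gives no abandonment rate, non-start rate or effect size, so there is no stated figure to reproduce. The check is algebra, followed by assumed rates.

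**Inputs from the document**
- Event: a gap of four or more weeks while on therapy (Table 3).
- Denominator: registered patients (Table 3), registered at first interaction (Intervention delivery). I take the base as the BL/Rb patients among them.
- Expected numbers: about 50 prospective and about 200 historical BL/Rb patients (Sample size and recruitment).

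**Inputs assumed**
- s = share who start treatment; c = risk of a four-week gap among starters. Deaths and referrals are ignored.

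**Formulas**
- Written measure: W = s×c.
- Inclusive measure (total loss): L = (1−s) + s×c.
- Hence L − W = 1−s, and between periods ΔL − ΔW = −Δs. The two changes differ by exactly the change in the share starting, whatever c does.

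**Main illustration, per 100 diagnosed children, c = 30% in both periods**

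| | Historical (s = 80%) | Prospective (s = 90%) | Change |
|---|---|---|---|
| Never start | 20 | 10 | −10 |
| Stop after starting | 80 × 0.30 = 24 | 90 × 0.30 = 27 | +3 |
| Written W | 24% | 27% | +3 points |
| Inclusive L | 20 + 24 = 44% | 10 + 27 = 37% | −7 points |
| Complete (100 − L) | 56% | 63% | +7 points |

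Check: ΔL − ΔW = −7 − 3 = −10 = −Δs.

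**Range.** I took c = 20%, 30%, 40% and 50%, with starts rising 60→90%, 70→90%, 80→90% and 80→95%. The written measure worsens by 2 points (0.80×0.20 = 16% to 0.90×0.20 = 18%) to 15 points (0.60×0.50 = 30% to 0.90×0.50 = 45%). The inclusive measure improves by 5 to 24 points.

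**When the drop-out risk also improves.** The written measure falls only if the new c is below s₀×c₀/s₁.
- Starts 80→90%, c₀ = 30%: 0.80×0.30/0.90 = 26.7%, a relative fall of more than 11.1%.
- Starts 70→90%, c₀ = 30%: 0.70×0.30/0.90 = 23.3%, a relative fall of more than 22.2%.
- Starts 70→90% with c falling from 30% to 27%: W goes from 21.0% to 0.90×0.27 = 24.3%, while L goes from 0.30 + 0.21 = 51.0% to 0.10 + 0.243 = 34.3%.

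**Starters-only denominator instead.** W becomes c, and non-starters vanish from both parts. If starts rise 70→90% and the added starters have a 50% risk, it reads 30% to (0.70×0.30 + 0.20×0.50)/0.90 = 34.4%.

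**Effect of consent on any inclusive measure.** Suppose nothing changes (s = 80%, c = 30%), but all 20 prospective non-starters leave before consent. The historical L is 44%. The prospective L is 24/80 = 30%, a spurious 14-point gain. The written measure moves from 24/100 = 24% to 24/80 = 30%, a spurious 6-point worsening.

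**The case against.** The strongest reply is that the next row of Table 3 already covers this. Completion is taken over registered patients, so a never-starter counts as a non-completer; in the illustration it rises from 56% to 63%. Read together, the two rows make a false conclusion less likely. That stands in part. But completion is a separate outcome that mixes in other reasons for not finishing, and it does not correct the abandonment figure on which Aim 2 relies.

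Second, the final clause of the definition might qualify only missed follow-up, not missed treatment. The wording allows this. Even so, nothing says that a child who never started counts, and chart abstractors and app users could then classify such children differently.

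Third, every rate is assumed, and the reversal needs drop-out among starters to stay nearly constant. This stands. With about 50 and 200 patients, the standard error of the difference in the illustration is √(0.24×0.76/200 + 0.27×0.73/50) ≈ 7 points, so a 3-point shift would be hard to see. The definition still determines what is being estimated.

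Two stronger readings are tempting and not supported:
- A reader might infer that the protocol contradicts its own definition of abandonment. The interview section lists contributing factors to explore; it does not define abandonment. It shows that starting treatment is relevant, no more.
- A reader might infer that mNavigator is built to persuade hesitant families to start. Intervention delivery does not place the educational videos before therapy, and it ties the pre-treatment checklists to protocol compliance. The Discussion puts health-system problems ahead of patient-centred ones. A rise in starts is possible, but it is not a stated mechanism.

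**Conclusion.** The point holds as a weakness in a fixed definition. On the plain reading of Table 3, diagnosed children who never start are in the denominator and cannot be events, so the written measure can move opposite to total loss. The gap between the two changes equals the change in the share starting: 10 points in the illustration (+3 against −7).

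This rests on registered BL/Rb patients being the base, on the final clause applying to treatment as well as follow-up, and on assumed rates. The documents do not show that starts will change, or in which direction, so they do not support a claim that abandonment will look worse or that any particular bias is present. The primary outcome is unaffected. It is worth correcting because the outcome serves a stated aim and the change is cheap.

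**What to change.** For outcome measurement only, and with no change to clinical management, report in both cohorts from the same starting point (BL/Rb diagnosis):

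- (a) never started planned treatment;
- (b) stopped for four or more consecutive weeks after starting;
- (c) the two combined.

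Classify death, referral and palliation separately, so that they do not become false events in (a) or (b). State the denominator, and the point at which a patient is classed as never started, identically for both cohorts.

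The Informed consent section limits prospective research data to consenting families but exempts historical data. A simple count over all diagnosed children could therefore inflate historical abandonment relative to the mNavigator period. Report the number of diagnosed patients lost before consent and interpret (a) and (c) in that light, or give a sensitivity analysis that counts them as never started.

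The cost is a short addition to Table 3 and derived variables from diagnosis, treatment and outcome records. The app is designed to record these, and the charts are to be abstracted into the same system. The downsides are higher reported abandonment rates and some missing start dates, since the historical abstraction takes only what the paper records hold.

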## Discussion

To our knowledge, mNavigator is the first digital health case management system specifically developed to improve health provider compliance with pediatric cancer treatment protocols in a low-resource setting.

The study has several strengths. First, mNavigator bolsters current standard of care by facilitating compliance with clinical best practices, promoting care coordination, and allowing simultaneous, ongoing quality of care evaluation. Currently at cancer centers in Tanzania, there is no mechanism to facilitate or monitor implementation of protocol-driven treatment in real time. Static paper-based medical records further prevent proactive actions to reduce treatment abandonment in pediatric cancer patients. A digital case management system such as mNavigator can dynamically identify and highlight instances of poor protocol compliance, errors in diagnosis or treatment, or patients lost to follow-up as compared to paper-based systems, which would require greater investments of human resources and time. By supporting allied health workers (nurses and patient navigator) in documenting patient cancer diagnosis and treatment data in mNavigator, patient-specific treatment plans are generated by the system which allows the implementation of treatment protocols via algorithms, checklists and alerts. As such, mNavigator promotes task shifting of lower-priority clinical tasks (e.g., measuring patients height/weight, data entry etc.) to ensure that the limited supply of highly trained physicians are used as efficiently as possible. This could reduce the clinical workflow burden for trained physicians and increase protocol compliance, reduce diagnostic delays, and improve quality of patient care.

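### Treatment abandonment is read from the same outcome form in both periods, but the form is filled from live follow-up in one and from paper charts in the other, so the difference is open to ascertainment bias

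*Protocol article*

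**What the plan says.** The section Outcome measures (Table 3) fixes three things about this secondary outcome.

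- Definition: "Treatment abandonment is defined as missing four or more consecutive weeks of treatment or follow-up while still on therapy". Death, transfer and unknown status are not mentioned.
- Contrast: "Calculated as the difference in proportion of patients registered in mNavigator who abandoned treatment compared to historical controls who abandoned treatment".
- Data source: the mNavigator outcome form, with no distinction between the periods.

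How the form comes to be filled is described elsewhere. In the prospective period, Intervention delivery lists among the users' tasks: "Follow-up with patients to record health related outcomes (on treatment, off therapy, relapsed disease, etc.) and vital status". It also has them enter referrals to outside hospitals. In the historical period, Quantitative data collection says that "trained research staff will abstract medical data into mNavigator from paper records for patients diagnosed with BL and Rb", and adds: "Items abstracted will include as many data points available in paper records that are included in mNavigator". No tracing or vital-status check of historical patients is described.

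The Discussion says that a digital system can pick out errors "or patients lost to follow-up as compared to paper-based systems", which it describes as needing more staff and time for the same task. Its limitations paragraph names the small samples, the single site and the historical controls, but not unequal measurement of outcomes.

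**The concern.** The tool that records the outcome is part of the intervention and was absent in the comparison period. The form has the same name in both periods, but what its author knows differs. A child who stops attending because of death at home or care elsewhere may leave only a gap in an old chart, and a gap of four weeks on therapy meets the definition as written. If the reason is learned through live follow-up in 2019–2020, the same gap may be entered as a death or a transfer. The two proportions would then differ with no change in behaviour.

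Reducing abandonment is named in Aim 2, and this is the outcome that Table 3 labels secondary. An artefact towards a fall would be read as benefit from mNavigator. One in the other direction could hide a benefit.

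**Working it through.** **Is there a figure to reproduce?** No. The article states no abandonment, death or transfer rate, no target difference and no significance level. It gives only the numbers of patients: about 50 prospective ("Of these, approximately 50 patients are anticipated to have a diagnosis of BL or Rb") and about 200 historical (50 records a year, 50 × 4 = 200). Every rate below, and the two-sided 5% level, is an assumption. True abandonment is taken to be the same in both periods.

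**Upper case.** Let s be the share who stop attending on therapy and f the share of those who in fact died or transferred. Suppose the prospective form captures all of these and the charts none. Historical abandonment then reads h = s, prospective reads p = s(1 − f), and the artefact is −s × f. The standard error is √[p(1 − p)/50 + h(1 − h)/200].

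| s | f | h | p | Artefact | SE | Ratio |
|---|---|---|---|---|---|---|
| 30% | 15% | 30.0% | 25.5% | −4.5 points | 6.96 | 0.65 |
| 30% | 33% | 30.0% | 20.1% | −9.9 points | 6.53 | 1.52 |
| 30% | 50% | 30.0% | 15.0% | −15.0 points | 6.00 | 2.50 |

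With s from 20% to 40% and f from 15% to 50%, the artefact runs from 0.20 × 0.15 = 3 points to 0.40 × 0.50 = 20 points.

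**Relaxing the upper case.** Let a be true abandonment, d deaths on therapy that are not abandonment, uP and uH the shares of those deaths left unrecorded (and so counted as abandonment) in the prospective and historical periods, and m the share of historical abandoners whom the chart does not reveal. Then:

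- prospective = a + d × uP
- historical = a(1 − m) + d × uH
- artefact = a × m + d(uP − uH)

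With a = 20%:

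| d | uH | uP | m | Historical | Prospective | Artefact | Chance of a false significant fall |
|---|---|---|---|---|---|---|---|
| 10% | 25% | 0 | 0 | 22.5% | 20% | −2.5 | about 5% |
| 20% | 50% | 0 | 0 | 30% | 20% | −10 | about 27% |
| 30% | 75% | 0 | 0 | 42.5% | 20% | −22.5 | about 87% |
| 20% | 50% | 25% | 0 | 30% | 25% | −5 | about 10% |
| 20% | 50% | 50% | 0 | 30% | 30% | 0 | 2.5% (nominal) |
| 20% | 50% | 0 | 25% | 25% | 20% | −5 | about 10% |
| 20% | 50% | 0 | 50% | 20% | 20% | 0 | 2.5% (nominal) |
| 10% | 25% | 0 | 25% | 17.5% | 20% | +2.5 | not calculated |

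Only the difference in the unrecorded shares matters, and abandonment hidden in charts works against it.

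**The planned completion rate.** A child who stops early is a non-completer whether labelled abandoned, died, transferred or unknown. In the first table, if those who stop attending are the only non-completers, completion is 100 − 30 = 70% in both periods in every row. Relabelling therefore leaves it unmoved, provided that a transferred child counts as a non-completer in both periods.

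**The case against.** A reader might infer that unrecorded deaths count as abandonment only in the historical arm and that a fall must therefore appear. The article does not support that, for four reasons.

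- Follow-up of vital status is listed among tasks done in later interactions with patients and caregivers. No telephone or home tracing of non-attenders is described, so prospective deaths may be missed as well.
- Nothing says that charts lack deaths or referrals. Under Intervention users, the four users have at least 2 years in the department and currently coordinate care, so they overlap part of 2015–2019.
- One Discussion sentence, "Static paper-based medical records further prevent proactive actions to reduce treatment abandonment in pediatric cancer patients", concerns preventing abandonment, not recording vital status. The sentence on patients lost to follow-up could even mean that more abandonment is detected prospectively.
- No text says that prospective patients who meet the four-week rule are reclassified when their vital status is known.

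All of this stands. It removes any fixed direction and any claim about size.

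A second objection is that the plan already holds a check. That also stands: the change in treatment completion rate, in the same table, is insensitive to this relabelling and is close to the complement of a composite of all early endings.

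A third is that a condensed article may leave coding rules to a fuller document. That is fair for the form's categories. It does not dispose of the point, because the article itself fixes the definition and a data source whose content differs by period. Used as written, these can give proportions that are not comparable.

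**Conclusion.** The concern holds in limited form. Abandonment is measured by a form whose information differs by design between the periods, and the definition does not say how death, transfer or unknown status is treated. The difference is open to ascertainment bias, most directly towards a spurious fall, but it may be smaller, nil or reversed.

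The size cannot be computed from the article. The 3 to 20 points rest on assumed rates of stopping, death and transfer, and on complete prospective and no historical capture, so they mark an upper case. Because the outcome is secondary, the completion rate is already planned and the repair is simple, this is a cheap improvement and not a flaw that undermines the study.

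**What to change.** For the between-period comparison, derive abandonment in both arms by one algorithm from recorded attendance and treatment dates, using the study's own four-week rule. Write down how death, transfer and unknown status are classified, and apply that identically in both arms. Report the outcome-form version as a sensitivity analysis. Present both beside the planned treatment completion rate, with non-completers in each arm broken down as abandoned, died, transferred and unknown.

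The cost is a little more derivation work. Some prospective deaths known only through follow-up contact will count as abandonment in the comparison, so that figure will look somewhat higher than the fullest data would show. The breakdown still displays what is known. The algorithm cannot repair charts that are missing or lack dates, so the number of such charts should be stated.
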